### Covariates

We will adjust in the analysis for Fagerström score, education level, income age and gender (cf. Haff et al., [32]). As a sensitivity analysis, we will also run the model without the covariates. Although we expect the majority of trainings to take place online due to COVID-19, some organizations may decide to offer them in person depending on the development of the current pandemic. The dichotomous variable online versus offline will therefore also be explored as covariate and treated similarly as above. Data will be analyzed according to the intention-to-treat principle.

### Secondary outcomes

Secondary outcomes for cessation after 13 and 26 weeks will be analyzed similar to the main model. Demographics, nicotine dependence, pack-years and regret proneness will be added as an interaction term with the allocation group to the main model to investigate effect modification. Using survival analyses, we will additionally use the SF-12 measure to explore if perceived health status influences relapse. Analyses are similar for medication use. The SASEQ scores are used to explore if self-efficacy is influenced by treatment (c.f. Van den Brand et al., [58]). We will also explore the determinants of self-efficacy of smoking at baseline with standard regression. Explorations for motivation to quit are similar. To further explore if regret proneness influences treatment effects, we will also perform a regression analysis within the lottery-arm, with abstinence at 13, 26 and 52 weeks as dependent variable and regret proneness, as well as covariates from the main model as independent variable.

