**Fig. 2 Fig2:**
[figure not shown]
Timeline of the Lotteries

The first lottery deadline is 1 week after the joint quitting moment in the third training. From the fourth training, lottery participants can win €50 every week for 13 weeks. The winner is drawn out of all participants within a group using the trial-ID, regardless of their smoking status. Participants only receive their prize if they did not smoke that week, as confirmed by the CO-measurement. Participants are informed by text message and email about whether they have won the prize and whether they receive their prize.

Lottery winners who need to forfeit their prize because they smoked, will learn about their forgone prize. All other participants will be informed about whether the prize is awarded or not, but not to whom. Every week offers a new chance to win, irrespective of prior performance. If the winner is not eligible for the prize, the money is forfeited. If the winner has previously withdrawn from the study, the notary will draw a new winner.

To summarize, when participants are selected as a winner, they are informed about this. Next, if they smoked in the week before the draw, they do not get the prize. Other participants are then also informed that the winner did not get the prize because he or she smoked.

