#### Weeks 14-26

After 26 weeks, all participants can win a family vacation voucher (worth €400). Again, the winners are drawn out of all participants within a group, regardless of their smoking status. The winner is always informed by text message and email. However, the winner only receives her prize if she was abstinent between weeks 14 and 26, as confirmed by the CO-measurement. If the winner is not eligible for the prize, a new winner is drawn until the prize can be awarded. All other participants will be informed that the prize is awarded or not, but not to whom.

The lotteries tested in this trial are distinct from conventional lotteries or quit and win contests because winning the lottery is not conditional on performance, but being able to claim the prize is. Participants are always in the drawing, irrespective of their performance. With this design, the lottery incentives take more the form of a commitment device [42], where people accept a presented deadline with the potential of finding out that they won a prize, but losing it because they did not stick to their own goal of not smoking.

As such, there are multiple design aspects that are meant to support people in achieving their own goal. First, the lotteries offer a vivid deadline with nearby consequences. This can help overcome an intrapersonal conflict between a farsighted *planner* that wants to quit smoking and shortsighted *doer* that wants to enjoy a cigarette. According to this model of self-control [43], people try to control their future myopic behavior to attain their long-term goals by restricting their future freedom of choice. Acceptance of a deadline with immediate feedback has been shown to achieve this [42, 44] and is therefore designed to obstruct the tendency to postpone the quitting attempt to enjoy a cigarette right now.

Second, people tend to overestimate their chances of winning a lottery [45]. Decision-making under risk is known to be influenced by emotional assessments of the outcomes and emotions at the time of the decision [46]. These emotions result in overweighting of small probabilities and especially for vivid outcomes [46]. As such, the potentially emotional effect of the lottery outcome is designed to increase the importance of the deadline.

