### Smoking abstinence carbon monoxide measurement

To biochemically verify smoking status, we use the validated non-invasive iCOquit Smokerlyzer® (Bedfont Scientific Ltd). The iCO measures CO-levels by requiring smokers to breath into the device. It is a strictly personal device that all participants receive by mail to their home address. Participants are asked to connect the device to their smartphone in order to use accompanied app. A tailored manual and instruction video was made for this trial and is sent to participants. Previous studies using smartphone CO-meters have shown personal mobile meters are suited to distinguish smokers from non-smokers and that usability is high [50, 51].

Participants receive a text message, asking them to perform and share the CO-measurement. After the measurement, results are presented in the app, that also allows participants to directly share their results with the trial staff via mail. Following the RS, we use a cut-off point of ≤9 ppm (p.p.m.) to determine smoking status. Measurements are weekly from the start of the training until 13 weeks after the quit date (of which 7 measurements are in the weeks of the training), and once at 26 and 52 weeks. Between weeks 14-26 there is one unannounced measurement. Participants know that it will ensue, but not in which week. If there is a difference between self-reported abstinence and biochemical validation or when participants do not respond, participants are assumed to have smoked. Following the RS, a failed biochemical test classifies a participant as smoking even when this is explained by the recent smoking of one to five cigarettes allowed throughout the follow-up period [49].

To summarize, when a participant reports not to have smoked more than five cigarettes between the quit-day and week 52, and this can be biochemically verified at week 52, they are considered not to have smoked. If previous measurements contradict this according to the criteria above, the participant is not considered continuously abstinent.

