An adjacent limitation is that unsuccessful participants might game the measurement by, for example, asking a non-smoker in their environment to breath into the device. In previous instances, CO-measurements were compared with urinary and salivary cotinine and only 4% of smokers reported falsely [68]. Likewise, even when there was a significant financial benefit in cheating, a trial with 604 participants found no differences between self-reports and CO-measurements [21]. We aim to prevent cheating by first asking to self-report smoking status and requiring the CO-measurement a day later and by stressing to participants that either smoking status (smoker or non-smoker) is acceptable to receive the study payment at the end of the study. At the main outcome point, there is also no financial incentive for cheating in either arm. By also using trusting and supporting langue throughout the trial (e.g., stating that relapse is never a personal failure), we aim to minimize this risk further.

A final limitation of the current study design is that it does not allow to disentangle the psychological mechanisms responsible for a potential effect. The lotteries host multiple components to leverage well-known influences on decision-making [26]. While we use surveys to explore perceptions and psychological constructs at work, trials with more than two treatment arms allow to vary more design characteristics to identify working mechanisms more precisely [69].

An important benefit of the current study design is the 6-month follow-up, after all lotteries have ended. A common pattern in the application of the current lotteries is that they especially support initial health behavior change, which declines after removal of the lottery deadlines [31, 32]. In contrast, research into smoking relapse curves suggest that not smoking might become ‘easier’ over time [41]. The present design allows us to explore which of the two patterns will be dominant.

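### At weeks 13 and 26 only the lottery arm has a financial reason to return a clean CO test, so counting every non-response as smoking may inflate those secondary effects

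*Protocol article*

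**What the plan says.** **Prizes.** In the lottery arm one winner per training group is drawn from all members, whatever their smoking status. For the weekly draws, "From the fourth training, lottery participants can win €50 every week for 13 weeks", and "Participants only receive their prize if they did not smoke that week, as confirmed by the CO-measurement" (Weeks 1 to 13). For the €400 voucher at week 26, "the winner only receives her prize if she was abstinent between weeks 14 and 26, as confirmed by the CO-measurement" (Weeks 14-26). Under Smoking abstinence self-reports, all lottery-arm measurements come before the winner is announced. The control arm has the same tests without prizes.

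**Classification.** Under Smoking abstinence carbon monoxide measurement, "when participants do not respond, participants are assumed to have smoked". No distinction is made by arm or time point. The same section says that earlier measurements that contradict the week-52 report, by the criteria given above it, remove continuous abstinence.

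**Analysis.** Continuous and point prevalence abstinence at weeks 13 and 26 are secondary outcomes, measured in the same way. Under Statistical methods, "Secondary outcomes for cessation after 13 and 26 weeks will be analyzed similar to the main model". The sensitivity analysis named there drops the covariates.

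**Interpretation.** Under Strengths and limitations: "At the main outcome point, there is also no financial incentive for cheating in either arm". The same section values the six months of follow-up after the lotteries, because effects might either fade or hold: "The present design allows us to explore which of the two patterns will be dominant".

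**The concern.** Counting non-response as smoking is usually defended as conservative. That defence concerns the level of abstinence in each arm. It does not protect the comparison between arms when the intervention itself rewards responding.

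A smoker who does not respond is classified correctly in either arm. An abstinent person who does not respond is classified wrongly. At weeks 13 and 26 an abstinent lottery participant who skips the test risks losing a drawn prize, while an abstinent control who skips it loses nothing. If that difference affects behaviour, more abstinent controls are misclassified and the comparison tilts toward the lottery.

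Two things are at stake. The week-13 and week-26 effects could mix abstinence with willingness to submit a test. Any reading of decline after the lotteries end would also compare a time point with a prize tied to testing in one arm against a time point with none. The reassurance about incentives covers only week 52, and only cheating.

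**Working it through.** **The plan's own figures.** Sample size: 57.5% v 22.6%, 90% power and alpha 0.05 (taken as two-sided) give 40 per arm; 40 × 1.35 = 54; 54 / 0.85 = 63.5, rounded up to 64. Prize cost: 13 × €50 + €400 = €1,050 per group of 8. All reproduce, and none is disputed.

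**Size of the incentive.** With 8 members, the expected value of being able to claim is €50 / 8 = €6.25 per weekly draw and €400 / 8 = €50 at week 26. The week-26 value is higher if others have relapsed, because that prize is redrawn until it can be awarded.

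**False difference with no true effect.** Let *p* be true abstinence, equal in both arms, and let *r*L and *r*C be the test return among abstainers in the lottery and control arms. Observed abstinence is *a* = *p* × *r*L and *b* = *p* × *r*C, so the false difference is *p* × (*r*L − *r*C). False clean tests are set to zero. Return rates are assumed, because the article gives none. The range for *p* spans the planning rates.

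Chance of p < .05, normal approximation: *n* = 64 / 1.35 = 47.4 per arm; *m* = (*a* + *b*) / 2; SE0 = √(2*m*(1 − *m*) / *n*); SE1 = √((*a*(1 − *a*) + *b*(1 − *b*)) / *n*); with *d* = *a* − *b*, the probability is Φ((*d* − 1.96 SE0) / SE1) + Φ((−*d* − 1.96 SE0) / SE1).

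| Return, lottery v control | *p* = 22.6% | *p* = 40% | *p* = 57.5% |
|---|---|---|---|
| 85% v 85% | 0 points; 5.0% | 0 points; 5.0% | 0 points; 5.0% |
| 90% v 85% | 1.1 points; 5.2% | 2.0 points; 5.5% | 2.9 points; 5.9% |
| 95% v 85% | 2.3 points; 5.9% | 4.0 points; 6.9% | 5.7 points; 8.6% |
| 95% v 75% | 4.5 points; 8.6% | 8.0 points; 12.9% | 11.5 points; 20.0% |

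Example: *p* = 40% and 95% v 85% give 38.0% v 34.0%, a difference of 4.0 points.

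**Weeks 26 to 52 with a constant true effect.** Assume true abstinence of 40% v 25% at both times (15 points, ratio 1.60), return of 95% v 85% at week 26, and 85% in both arms at week 52, independent of week 26.

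- Week 26: 0.40 × 0.95 − 0.25 × 0.85 = 0.380 − 0.2125 = 16.8 points; ratio 1.79.
- Week 52, earlier missed tests not counted: (0.40 − 0.25) × 0.85 = 12.8 points; ratio 1.60. This is an apparent decline of 4.0 points with no relapse behind it.
- Week 52, earlier missed tests counted: 0.85 × (0.380 − 0.2125) = 14.2 points; ratio 1.79. There is no decline on the ratio scale, but the week-26 asymmetry now sits in the week-52 result.

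The criteria for a contradicting earlier measurement include non-response, so the text can be read either way.

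**The case against.** **The incentive is modest and indirect.** A reader might infer that a clean test earns a prize. It does not: the draw ignores smoking status, and the test only lets a drawn winner keep the prize, worth on average about €6.25 per weekly draw. This stands, and it is a reason not to presume a large return gap.

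**Both arms are treated alike otherwise.** They have the same tests, the same reminders and the same €30 regardless of smoking status. The self-report a day before the CO test, the unannounced test, and the cited 604-participant trial that found no difference between self-report and CO are also relevant. The shared measures should raise return in both arms but do not remove the asymmetry. The other three mainly address false clean tests, not missed ones.

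**Fade-out is not a specified analysis.** The Discussion says only that the design allows the pattern to be explored, and Statistical methods defines no contrast between weeks 26 and 52. This stands. The request is for cautious interpretation, not for a new model on which the statement must rest.

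**A condensed article may leave missing-data analyses to an SAP.** This is fair, and an SAP that is not shown may contain them. The absence of such analyses is therefore not the point. The article itself fixes the classification rule and carries it to time points where the incentive differs by arm.

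**Conclusion.** The concern holds as a risk to the week-13 and week-26 secondary outcomes. The asymmetric incentive, the common non-response rule and the direction of any resulting bias follow from the text. Whether bias occurs, and how much, depends on return rates among abstainers that the documents do not give. Under assumed gaps of 5 to 20 points the false difference is about 1 to 12 points, against a planned difference of about 35. With equal return and no false clean tests it is zero.

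Two stronger readings are tempting, and the documents support neither. The first is that the week-13 and week-26 effects are partly artefact; only *may be* is justified. The second is that a decline after week 26 would be spurious. That needs the return gap and also the reading under which earlier missed tests do not count at week 52. On the other reading the asymmetry carries into week 52 instead, and the article does not settle which applies. The sample size calculation is unaffected.

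**What to change.** 1. Keep the Russell Standard analysis at weeks 13, 26 and 52.
2. Report the return of valid CO tests and of self-reports by arm at all three time points.
3. At weeks 13 and 26, add a sensitivity analysis that does not equate non-response with smoking and that varies the odds of smoking among non-responders separately by arm. Imputation from the weekly texts and CO values helps mainly at week 13. The weekly series stops there, leaving one unannounced test before week 26, so the week-26 result will rest more on the assumed odds.
4. State whether earlier missed tests count against week-52 continuous abstinence.
5. Interpret any decline after the lotteries end alongside these results.

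The cost is wording and a little more analysis of data already being collected. The downside is that the week-13 and week-26 results may look less favourable and less certain.

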### Sample size calculation

In a meta-analysis, Haff et al. [32] analyzed lottery trials targeted at various health behaviors, with a pooled success percentage of 57.5% in the lottery condition versus 22.6% in the control condition. A sample size calculation for detecting a 0.35 difference between proportions at *p* < .05 and a power (1-*β*) of 90%, indicated a sample size of 40 per condition. With an intra-class correlation coefficient of .05, based on a CRT by Van den Brand and colleagues [21] and an estimated cluster size *m* of 8, a design effect (1 + (*m*-1) x ICC) of 1.35 an effective sample size of 54 per condition was estimated. We aim to recruit a minimum of 64 participants per condition (meaning 8 clusters per condition), allowing 15% participant attrition over time. Based on the power calculation, we aim to assign 16 clusters to receive either a smoking-cessation training or a smoking-cessation training plus the smoke-free lottery.

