### Effect modifiers

We will explore multiple effect modifiers and gradually build up the models to determine which has the most parsimonious fit. To determine whether regret plays a role in any potential effect, regret proneness is measured via the translated Regret Scale [56]. We use the first question of the Dutch version of the SF-12 as a generic measure of health status [57]. The SF-12 is used to explore the effect of health status on relapse rates. Similar to health status, we will explore the effect of self-reported medication use (yes-no) on relapse rates. If variables moderate the effect, results are also presented separately per group. An overview of all measures is given in Table 1.

**Table 1 Tab1:** Overview of measurements

Measurements	T0 baseline	T1-T2 weeks 1-13	T3 week 26	T4 week 52
Demographics	▲			
Generic health status (SF-12)	▲	▲	▲	▲
Self-efficacy of smoking abstinence (SASEQ)	▲	▲	▲	▲
Motivation to quit (TSRQ)	▲			
Pack-years	▲			
Regret Scale	▲			
Nicotine dependence (FTND)	▲			
Smoking self-reports (text message; RS)	▲	▲	▲	▲
CO-measurements (Smokerlyzer)	▲	▲	▲	▲

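### The lottery-arm-only regression on regret proneness cannot show whether regret proneness changes the treatment effect, because its slope adds prognosis and effect modification together

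*Protocol article*

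**What the plan says.** The protocol article plans two analyses of regret proneness under Statistical methods, Secondary outcomes.

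- **Two-arm analysis.** With demographics, nicotine dependence and pack-years, "regret proneness will be added as an interaction term with the allocation group to the main model to investigate effect modification".
- **Lottery-arm analysis.** "To further explore if regret proneness influences treatment effects, we will also perform a regression analysis within the lottery-arm". The outcome is abstinence at each of the three follow-ups (weeks 13, 26 and 52), and the predictors are regret proneness and the main model's covariates.

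Under Effect modifiers, the reason for collecting the scale is given as: "To determine whether regret plays a role in any potential effect, regret proneness is measured via the translated Regret Scale". Table 1 marks the Regret Scale at baseline only and restricts it to neither arm. By contrast, the questions on attitudes to the lotteries are put to the lottery arm alone (Data collection, Secondary outcomes). The effect-modifier work as a whole is exploratory: "We will explore multiple effect modifiers and gradually build up the models to determine which has the most parsimonious fit".

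**The concern.** Whether a baseline trait influences a treatment effect is a question about a difference between arms: is the gap in abstinence between lottery and control larger for regret-prone smokers than for others? The second regression drops the control arm, so it cannot contain that gap. Regret-prone smokers might quit more often, or less often, whatever they are offered. Within the lottery arm this looks the same as a stronger or weaker response to the lottery.

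Anticipated regret is the central rationale of the lottery design. A slope found in the lottery arm, under the purpose the plan gives it, invites the reading that the lottery works better in regret-prone people. The two-arm interaction may well be inconclusive at this sample size. A null interaction beside a significant single-arm slope is then a plausible result, and the present wording lets the second be taken as support.

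**Working it through.** **The plan's own figures.** The article gives no calculation for the regret analyses, so I first reproduced the sample size that they inherit (Sample size calculation).

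- Inputs: the rates, "with a pooled success percentage of 57.5% in the lottery condition versus 22.6% in the control condition", and "power (1-*β*) of 90%, indicated a sample size of 40 per condition". Alpha is 0.05. Sidedness is not stated; two-sided reproduces the figure.
- Formula (pooled variance, no continuity correction): n = [z(0.975)·√(2p̄(1−p̄)) + z(0.90)·√(p1(1−p1) + p2(1−p2))]² / (p1−p2)².
- Numbers: p̄ = 0.4005 and p1−p2 = 0.349. The numerator is (1.960×0.693 + 1.282×0.648)² ≈ 4.79. Then 4.79/0.1218 ≈ 39.3, rounded up to 40.
- Design effect 1 + 7×0.05 = 1.35, and 40×1.35 = 54. With 15% attrition, 54/0.85 = 63.5, rounded up to 64. All three figures agree with the article.

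**What each regression estimates.** Write T for allocation (1 = lottery), R for standardised regret proneness and Y for abstinence:

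logit P(Y) = b0 + b1·T + b2·R + b3·T·R

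- Slope of R in the control arm: b2 (prognosis).
- Slope of R in the lottery arm: b2 + b3.
- Effect modification on the odds-ratio scale: b3.

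The lottery arm alone gives b2 + b3, and no amount of data from that arm separates the two terms. Reading the slope as b3 requires b2 = 0, which the article neither states nor justifies.

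**Size, by simulation.** From the article: 64 per arm, clusters of 8, ICC 0.05, rates of 22.6% and 57.5%. Assumed, because the article gives none: the odds ratios (OR) for regret proneness per SD. There were 2,000 runs per row, with plain logistic fits and no further covariates. The lottery-arm and interaction ORs are medians over runs, and *significant* means p < 0.05.

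| Control-arm OR per SD, exp(b2) | Interaction OR, exp(b3) | Lottery-arm OR | Lottery-arm slope significant | Estimated interaction OR | Interaction significant |
|---|---|---|---|---|---|
| 1.0 | 1.0 | 0.98 | 4.6% | 1.00 | 5.2% |
| 1.5 | 1.0 | 1.50 | 30.3% | 1.01 | 4.8% |
| 2.0 | 1.0 | 1.97 | 66.2% | 0.96 | 5.4% |
| 1.0 | 2.0 | 1.99 | 67.4% | 2.00 | 36.6% |
| 0.5 | 2.0 | 1.00 | 4.2% | 2.06 | 37.6% |
| 0.67 | 1.5 | 1.00 | 4.6% | 1.52 | 17.4% |

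- Rows 3 and 4 give nearly the same lottery-arm result (OR 1.97 and 1.99; 66.2% and 67.4%), yet one has no modification and the other has only modification.
- Rows 5 and 6 contain real modification, and the lottery-arm slope shows none of it.
- In rows 1 to 3, with no modification, the interaction test stays between 4.8% and 5.4%.

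**Hand check of the 30%.** With an assumed 35% abstinent, SE(log OR) ≈ 1/√(64×0.35×0.65) = 0.262. Then z = ln(1.5)/0.262 = 0.405/0.262 = 1.55, and P(Z > 1.96 − 1.55) ≈ 0.34. This is the same order as the simulated 30.3%, at a different abstinence rate.

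**The case against.** The strongest reply is that the valid analysis is already planned, and comes first in the same paragraph. The lottery-arm regression is offered as an additional exploration and replaces nothing. The lottery-arm slope is also a legitimate component of the two-arm contrast, and reporting it beside the control-arm slope is good practice. Under Strengths and limitations, moreover, the article concedes that its design cannot separate the psychological mechanisms. All of this stands, and it limits the seriousness of the point. It does not rescue the stated purpose: calling an analysis exploratory does not make b3 estimable from one arm.

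Stronger readings are tempting, and the article does not support them.

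- *Effect modification by regret has no proper test.* It has one: the planned interaction.
- *The lottery-arm regression is meant to prove that the lottery works through regret.* The text only proposes to explore, and nothing says that a slope would be reported as proof.
- *The slope is purely prognostic.* It is a mixture of prognosis and any modification.
- *The regression ignores clustering.* The sentence is silent on this, while Strengths and limitations says clustering has to be handled in the models. Such detail may sit in a fuller plan.
- *The 30% and 66% are inflated type I error.* They are the power to detect a real, assumed prognostic association. They become false claims of modification only if the slope is read as the purpose phrase invites.

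**Conclusion.** The point holds for one sentence of the plan. The lottery-arm regression cannot answer the question assigned to it, because its slope is b2 + b3 while the question concerns b3. That follows from the model and does not depend on any assumed value.

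The practical size does depend on assumptions. With no modification and 64 lottery participants, the slope is significant in about 5%, 30% and 66% of trials at prognostic odds ratios of 1.0, 1.5 and 2.0 per SD. If regret proneness is unrelated to quitting in the control arm, the slope does not mislead in this way; the article gives no information on that.

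The primary outcome, the primary model, the sample size and the planned interaction are unaffected. This is a real but contained error of purpose in a secondary, exploratory analysis, and it is worth correcting before results are reported.

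**What to change.** 1. State that any conclusion on effect modification by regret proneness, at weeks 13, 26 and 52, rests only on the allocation-by-regret interaction in the multi-level model.
2. From that model, report the regret slope with its confidence interval in both arms, alongside the interaction and its interval.
3. Relabel the lottery-arm regression as *predictors of abstinence among lottery participants*, and remove the reference to treatment effects from its purpose.

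The cost is wording only. The plan already needs the Regret Scale in both arms for its interaction, so no data collection changes. The drawback is imprecision: under the assumed values, the interaction is detected in about 17% of trials at an interaction odds ratio of 1.5 per SD and about 37% at 2.0. The report must say so, and must not take a non-significant interaction as evidence that regret proneness is irrelevant.
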